## Methods/design

### Study design and ethical aspects

This non-inferiority randomized controlled clinical trial, with two parallel groups with 1:1 allocation ratio was reported according to the Standard Protocol Items for Clinical Trials (SPIRIT) and then registered on the ClinicalTrials.gov platform (NCT03785730). The protocol was approved by the Research Ethics Committee of Universidade Ibirapuera (UNIB). The other centers involved are considered co-participants (Centro Universitário do Norte—Uninorte, Centro Universitário Uninovafapi—UNINOVAFAPI, and School of Dentistry from the University of Sao Paulo—FOUSP).

Children aged 3 to 6 years with at least one proximal cavitated lesion on anterior primary teeth will be selected. Teeth will be randomly allocated to selective removal of carious tissue and resin composite restoration (RCR) or NRCC. Tooth survival after two years of follow-up will be the primary outcome and cost-effectiveness, satisfaction, and discomfort reported by participants and parents/guardians’ perception will be the secondary outcomes.

Only patients who fulfill the eligibility criteria will be included in the study after the legal guardians sign the informed consent form and the child consents to participate in the study.

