### Data collection and evaluated outcomes

All data obtained will be tabulated by a researcher and checked by another researcher. An identifying number will ensure participants' confidentiality. The data will be stored on the cloud with access restricted to the researchers involved in the project and the principal investigator. After completing the study and data deidentification, the data will be used in an open electronic database to ensure research transparency. Due to the short follow-up, there will be no data monitoring committee. However, the coordinator of the trial will be responsible for periodical auditing.

The explanatory variables—sex, age, toothbrushing, use of fluoride toothpaste, and dental floss—will be collected by a questionnaire with closed-ended questions. Tooth survival after two years of follow-up will be considered as the primary outcome. Secondary outcomes will be the cost-effectiveness of both treatments, satisfaction, and discomfort reported by participants and parents/guardians' perception.

Patients will be contacted by telephone for recall of the periodical appointments. For those who cannot be contacted after several phone call attempts, a letter will be sent to the home address.

Four examiners will be trained for the assessed outcomes in two stages:Theoretical classes with images (three hours).Clinical setting with children with similar conditions to the eligible ones, but not included in the study (three hours).

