#### Discomfort reported by participants

The participant will be questioned about the discomfort related to the intervention immediately after the treatment is finished using the Face Image Scale (FIS) [14]. The scale will be shown to the children and they will be asked to point to the image that represents their discomfort level after the question: how do you feel at this moment? Without the operator’s presence, the dental assistant will ask for the participant’s most honest opinion.

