#### Satisfaction of the participants

The treatment satisfaction of the participants will be rated using a close-ended questionnaire six months from the initial treatment. To each question, the participants will be asked to point the image that represents their feelings. The FIS scale will be used as explained above.

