### Data analysis

The efficacy of each treatment will be evaluated according to five main outcomes:Tooth survival (primary outcome): The outcome will be dichotomized as survival versus failure. Kaplan Meier’s plot with overall survival in intention-to-treat (ITT) study population will be performed. The ITT study population will include all randomized participants regardless of protocol deviations, non‐compliance, or early study withdrawal. The Log-Rank test will be used to compare the survival curves of the two groups. The multivariate Cox regression with shared frailty model will be used to evaluate the influence of the explanatory variables (sex, age, jaw, type of teeth, toothbrushing, use of fluoride toothpaste, and dental floss) on the outcome. Hazard ratios (HR) with the respective 95% confidence interval will be calculated.Cost-effectiveness (secondary outcome): Incremental cost-effectiveness ratio will be calculated considering the ratio between the total cost of each treatment and tooth survival after two years.Discomfort reported by the participants (secondary outcome): The data will be summarized as the mean with the standard deviation or the median with the interquartile range, as appropriate. The two groups will be compared after confirming the distribution of data (Normal/non-normal), using the Student's t-test or Mann–Whitney test.Satisfaction of the participants (secondary outcome): The data will be summarized as the mean with the standard deviation or the median with the interquartile range, as appropriate. The two groups will be compared after confirming the distribution of data (Normal/non-normal), using the Student's t-test or Mann–Whitney test.Perception of the Parents/Legal Guardians (secondary outcome): The data will be summarized as the frequencies. The two groups will be compared using the Chi-Square Test.

For all analyzes, the significance value will be set at 5%.

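### Discomfort and satisfaction face scores: a normality check that settles nothing selects an unadjusted test, and age, already collected, is left unused, which may cost some precision

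*Protocol article*

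**What the plan says.** The Data analysis section of the protocol article gives discomfort and satisfaction the same analysis. Scores are summarised by mean and standard deviation or by median and interquartile range, and then "The two groups will be compared after confirming the distribution of data (Normal/non-normal"), "using the Student's t-test or Mann–Whitney test". No covariate is named for either outcome.

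For discomfort, the children see the Face Image Scale straight after treatment and "they will be asked to point to the image that represents their discomfort level". Satisfaction is asked at six months through several closed questions, and "The FIS scale will be used as explained above". The article does not state the number of faces.

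On age, the Study design section says "Children aged 3 to 6 years with at least one proximal cavitated lesion on anterior primary teeth will be selected". The Data collection section lists "sex, age, toothbrushing, use of fluoride toothpaste, and dental floss" as explanatory variables that "will be collected by a questionnaire with closed-ended questions". In the analysis, age appears once, in the model for tooth survival: "The multivariate Cox regression with shared frailty model will be used to evaluate the influence of the explanatory variables (sex, age, jaw, type of teeth" and further items).

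**The concern.** Two features of this analysis can be improved.

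- **The normality step.** One answer on a face scale is an ordered category and cannot be normally distributed. A check with a foregone result is not a rule for choosing a test. Satisfaction has several questions. If they are combined into a total, the check could go the other way, and the two outcomes could end up with different summaries and different tests. Whether the comparison is of means or of ranks would then be decided by the data.
- **Age.** Answers to a face scale plausibly shift between 3 and 6 years. If they do, part of the spread in the scores is explained by a variable the trial already holds, and neither candidate test can use it.

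At stake is some precision and a clearly defined effect measure for two secondary outcomes. The primary outcome is not affected.

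**Working it through.** **The plan's own figure.** The only sample size stated is for tooth survival. With 89.7% survival in both arms, a 15-point margin, one-sided 5% and 80% power:

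n per arm = (1.645 + 0.842)² × 2 × 0.897 × 0.103 / 0.15² = 50.8, so 51 per arm and 102 teeth.

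102 × 1.2 × 1.2 = 146.9, or 73.4 per arm, rounded up to 74 per arm and 148 teeth. The stated figures reproduce. The article gives no power, standard deviation or target difference for discomfort or satisfaction.

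**Assumptions for what follows.** Five faces, two-sided 5%, 60 or 74 independent scores per arm, and an age–score correlation ρ. None of these is given in the documents for these outcomes; 74 is the planned number of teeth per arm.

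**Step 1: gain from age by formula.** Adjustment multiplies the residual variance by (1 − ρ²). With 74 per arm, the difference detectable at 80% power without adjustment is (1.960 + 0.842) × √(2/74) = 0.461 SD. With adjustment it becomes 0.461 × √(1 − ρ²), and power at the original difference becomes Φ(2.802/√(1 − ρ²) − 1.960).

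| ρ | Variance removed | Detectable difference (SD) | Power |
|---|---|---|---|
| 0 | 0% | 0.461 | 80.0% |
| 0.1 | 1% | 0.458 | 80.4% |
| 0.2 | 4% | 0.451 | 81.6% |
| 0.3 | 9% | 0.439 | 83.6% |
| 0.4 | 16% | 0.422 | 86.4% |
| 0.5 | 25% | 0.399 | 89.9% |

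**Step 2: simulated ordinal scores, rank-based adjustment.** Face probabilities at mid-age in one arm were 0.40/0.25/0.17/0.11/0.07, with 74 per arm, an arm odds ratio of 0.45 at a given age, and 6,000 runs per setting.

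| Age–score correlation (size) | Power without age | Power with age |
|---|---|---|
| 0 | 73.5% | 73.4% |
| 0.17 | 70% | 71% |
| 0.28 | 68% | 71% |
| 0.37 | 63% | 70% |
| 0.45 | 57% | 68% |

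Type I error stayed near 5% with and without age. The last row needs a log-odds of −0.9 per year, that is an odds ratio of exp(−2.7) = 0.07 across the three years from 3 to 6.

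**Step 3: the planned two-stage rule against linear adjustment for age.** Three shapes of face distribution, 60 per arm, 2,000 runs per setting.

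- At ρ = 0.3, power of the planned rule against the adjusted analysis was 0.72 and 0.75, 0.75 and 0.78, 0.70 and 0.72.
- At ρ = 0.5 it was 0.73 and 0.82, 0.73 and 0.83, 0.70 and 0.81.

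**Step 4: what the normality check does.** In the same runs Shapiro–Wilk rejected normality in 100% of samples, so the rule always led to Mann–Whitney. Its type I error was 0.040 to 0.050, and its power was within about 1.5 points of the t-test. The check neither changes the test used for a single item nor costs meaningful power.

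**The case against.** **Adjustment is optional.** An unadjusted comparison is valid under randomisation, and both outcomes are secondary. This stands. It makes the point an improvement and not the correction of an error.

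**The gain is not established.** A reader might infer that the plan certainly throws precision away. The documents do not support that: they give no age–score correlation, and at 0.2 or below the gain is negligible. The largest gains need a steep age effect for which the documents offer no evidence. This stands, so the loss is stated only as possible, with its range.

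**The normality check does no harm to power.** A reader might also infer that the check causes the loss. Step 4 shows that it does not. If it always rejects, the discomfort test is in effect fixed. What remains is a specification weakness: the step is empty for a single item and could steer a combined satisfaction score to a different test.

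**Reporting.** The article names no effect estimate for these outcomes, but a condensed article may leave this to the full protocol or analysis plan, so its absence is not counted as a fault. Nor does the article assert that non-restorative cavity control causes less discomfort. Its Discussion speaks only of a potential for this.

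**Age alone is an incomplete choice.** Centre is the stratification factor. Teeth are randomised and a child may contribute several, while the scores come from the child. Independent-sample tests ignore this, and so do the calculations above. Clustering may matter more than age. This stands and widens the fix. In addition, a proportional-odds ratio adjusted for age is not the same quantity as the unadjusted one, so the adjusted effect must be named in advance as the target.

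**Conclusion.** The point holds as a free improvement to two secondary outcomes. The article fixes an unadjusted test selected by a normality check. On a single few-category face item that check practically always rejects and so decides nothing. Age is collected and not used.

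The possible gain from using it is at most about 2 power points for correlations up to 0.2, about 3 to 4 at 0.3, and about 10 at 0.45 to 0.5, with no material loss if age is irrelevant. These figures rest on five faces, an assumed correlation and independent scores. With fewer independent children than teeth, absolute power would be lower than shown.

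The planned test remains valid under randomisation apart from clustering by child. Neither a proven loss of precision nor a loss caused by the normality check can be concluded.

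**What to change.** In the Data analysis section, for both discomfort and satisfaction:

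1. Delete the distribution check and the choice between t-test and Mann–Whitney.
2. Prespecify one model for both outcomes, either ordinal (proportional-odds) or rank-based, with arm, age and the stratifying centre.
3. Allow for clustering by child where a child contributes more than one tooth, for example by a random effect or cluster-robust standard errors in the ordinal model. State how a child's score is assigned to an arm if that child has teeth in both.
4. State how the several satisfaction questions are combined or analysed.
5. Report the effect estimate with its 95% confidence interval; for the ordinal model this is the common odds ratio.

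The cost is analysis wording only. Age and centre are already recorded, and no extra data, visits or participants are needed.

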This study aims to evaluate the impact of NRCC for proximal carious lesions in anterior primary teeth on teeth survival. The secondary outcomes will be cost-effectiveness and patients-centered outcomes between the two treatment options. We hypothesize that the survival of teeth treated with NRCC is non-inferior, with a non-inferiority margin of 15%, from that of teeth restored with composite resin.

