### Sample selection

For sample size calculation, we used an expected survival of primary teeth with cavitated lesions in dentin affecting the proximal surface submitted to NRCC of 89.7% after 24 months [13] and a clinically significant difference of 15% in the success rate between groups. Considering a non-inferiority study, a significance level of 0.05 and a power of 0.80, we reached the final number of 102 teeth. Since each child can contribute with more than one tooth, 20% was added to this value (cluster per child), and 20% more was added due to possible sample losses. Thus, the final rounded number of 74 teeth per group was reached, resulting in a total of 148 teeth (sealedenvelope.com).

Children aged 3 to 6 years will be selected from the Clinical Pediatric Research Center—UNIB (CEPECO) (São Paulo, SP, BR), Pediatric Dentistry Clinic—Uninorte (Manaus, AM, BR), Pediatric Dentistry Clinic—UNINOVAFAPI (Teresina, PI, BR) and dental trailer (FOUSP) located on Educational Complex [name] de Lima (Barueri, SP, BR). The screening will be carried out under natural light with the aid of a wooden spatula. Potentially eligible children will be referred for clinical examination.

Recruitment will be taking place from April 2019 to December 2021. After allocation and treatment, the children will be followed up for 24 months. Table 1 displays the flow diagram of the clinical trial phases.

**Table 1 Tab1:** Flow diagram of clinical trial’s phases in according to SPIRIT

Timepoint**	Study period						
	Enrolment	Allocation	Post-allocation				Close-out
	*−t*_*1*_	0	*t*_*1*_	*t*_*2(6 m)*_	*t*_*3(12 m)*_	*t*_*4(18 m)*_	*t*_*5(24 m)*_
*Enrolment*							
Eligibility screen	X						
Informed consent	X						
Allocation		X					
*Interventions*							
NRCC			X				
RCR			X				
*Assessments*							
Survival of tooth				X	X	X	X
Cost-effectiveness			X				X
Discomfort reported by participant			X				
Satisfaction of the participants				X			
Perception of the Parents/legal Guardians		X	X	X			

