#### Perception of the parents/legal guardians

The perception of the parents or guardians concerning the treatment will be evaluated by the "Child's and parent's questionnaire about teeth appearance" [15] applied before the treatment, immediately after, and six months later. The dental assistant alone will ask for their honest opinion.

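### If the parents' questionnaire has graded answers, the planned chi-square test ignores their order; an order-using analysis would be a cheap, minor improvement to this secondary outcome.

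*Protocol article*

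**What the plan says.** The protocol article lists parents'/guardians' perception as a secondary outcome and counts it among the five main outcomes in Data analysis. The section on perception of the parents/legal guardians names a published questionnaire about teeth appearance, "applied before the treatment, immediately after, and six months later". It does not give the number of items, the answer options, whether they are ordered, or whether a score is formed.

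The analysis is fixed in Data analysis: "The data will be summarized as the frequencies. The two groups will be compared using the Chi-Square Test". No trend test, rank test or ordinal model is named for this outcome.

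For the children's discomfort and satisfaction, the same section plans means or medians, and then: "The two groups will be compared after confirming the distribution of data (Normal/non-normal), using the Student's t-test or Mann–Whitney test". Both of those outcomes are recorded on the Face Image Scale; for satisfaction the article says "To each question, the participants will be asked to point the image that represents their feelings. The FIS scale will be used as explained above". A 5% significance level applies throughout, and no effect size or power is stated for any secondary outcome.

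**The concern.** A Pearson chi-square test on a table of arms by answer categories gives the same p-value however the categories are arranged. With graded answers, that spreads its sensitivity over every possible pattern of difference, whereas the question here has a direction: do parents rate the appearance better or worse when a front tooth is left unrestored? A test that uses the order concentrates on that shift.

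At stake is the chance of detecting a real shift in parents' perception, and the reporting of its size. The chi-square statistic comes with no estimate or confidence interval. Parents' acceptance is part of the trial's stated rationale, so an estimate of the difference would be more useful than a bare p-value.

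**Working it through.** **1. The plan's own figure.** The article gives no power for perception. Its only sample-size figure is for tooth survival, and it reproduces. The inputs are survival "submitted to NRCC of 89.7% after 24 months" (taken for both arms), a difference of 15 percentage points, power 0.80, and 0.05 taken as one-sided:

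- n per arm = (1.645 + 0.842)² × 2 × 0.897 × 0.103 / 0.15² = 6.18 × 0.1848 / 0.0225 = 50.8, so 51 per arm and 102 teeth.
- 51 × 1.2 × 1.2 = 73.44, so 74 per arm and 148 teeth.

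These numbers count teeth. The number of parents is not stated and may be smaller, since one child can contribute several teeth.

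**2. Analytic comparison.** Assumptions: two-sided 5% (sidedness is not stated for this outcome), k ordered answer levels, and a one-directional shift that an ordered 1-df test captures fully. An ordered test with 80% power has non-centrality (1.96 + 0.8416)² = 7.85. The unordered test has about the same non-centrality on k − 1 degrees of freedom:

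| Levels | df | 5% critical value | Chi-square power | Loss against 80% |
|---|---|---|---|---|
| 2 | 1 | 3.84 | 80.0% | 0 |
| 3 | 2 | 5.99 | 70.9% | 9.1 points |
| 4 | 3 | 7.81 | 64.5% | 15.5 points |
| 5 | 4 | 9.49 | 59.5% | 20.5 points |

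The gap does not depend on the ordered test reaching 80%. At 50%, 60%, 70% and 90% power for the ordered test, the loss is 9.9, 10.5, 10.3 and 6.5 points for 3 levels; 15.5, 16.8, 16.9 and 11.6 for 4 levels; and 19.2, 21.1, 21.8 and 16.0 for 5 levels.

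**3. Simulation.** 20,000 runs per scenario, Pearson chi-square against tie-corrected Mann-Whitney, proportional-odds shift, independent observations. With answers spread evenly and an odds ratio of 2 (an assumption; the article gives none):

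| Levels | 51 per arm | 62 per arm | 74 per arm |
|---|---|---|---|
| 3 | 36.7% vs 46.6% | 43.5% vs 53.5% | 51.9% vs 62.1% |
| 4 | 33.5% vs 48.4% | 40.0% vs 56.7% | 47.7% vs 64.8% |
| 5 | 29.3% vs 49.6% | 37.0% vs 58.1% | 42.9% vs 65.0% |

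(Chi-square first, Mann-Whitney second.) Fewer respondents lower both figures but do not close the gap. For a yes/no item at 74 per arm the two tests agree (55.1% vs 55.0%).

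Over odds ratios of 1.5 to 3, even, symmetric and skewed answer patterns, and 51 to 74 per arm, the loss for 3 to 5 levels runs from 3.8 to 23.9 points. With the yes/no case included, the range is 0 to about 24.

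**4. Validity.** With no true difference, both tests rejected in 4.4% to 5.9% of runs. The chi-square test is therefore valid, and the issue is efficiency only.

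**5. Where chi-square does better.** With five levels at 0.20 each in one arm and 0.30/0.15/0.10/0.15/0.30 in the other, 74 per arm, chi-square has 50% power and the rank test 5%.

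**The case against.** The strongest objection is that the premise is not in the article. The answer format sits in a cited questionnaire that is not at hand. If the items are yes/no or nominal, chi-square is suitable and nothing is lost. This stands, and it is why the point can only be conditional. A reader might infer that the plan throws away a fixed 9 to 21 points of power; the documents do not support that.

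A reader might also infer an internal inconsistency, because discomfort and satisfaction are compared "using the Student's t-test or Mann–Whitney test". The article does not show one. Those outcomes use the Face Image Scale, whereas perception uses a different instrument, and different data types can justify different tests. Nor does the plan commit to a rank test for them, since it chooses between two tests by distribution.

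A third tempting reading is that a significant chi-square result would leave the direction unknown. The frequencies by arm are planned and would show it. What is missing is an effect estimate with its uncertainty. Likewise, nothing in the article says that a non-significant result will be reported as equal acceptance.

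It is also fair to say that 74 per arm counts teeth rather than parents, that the odds ratios are assumed, and that the calculations treat answers as independent. These limit the absolute power figures. They do not remove the gap between the two tests for graded answers under a one-directional shift.

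Finally, item-level test choice is often left to an analysis plan. Here, however, the article does name the test, so a comment on that choice is in order.

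**Conclusion.** The point holds conditionally. If items have three or more graded answers and the arms differ by a one-directional shift, the planned test costs about 9, 15 or 20 points of power for 3, 4 or 5 levels where an ordered test would have 80%. The loss is about 0 to 24 points over reasonable assumptions and 0 for yes/no items. The figures assume two-sided 5%, a proportional-odds shift and independent responses.

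There is no bias and no inflation of type I error, and the primary outcome is untouched. This is a minor, inexpensive improvement to one secondary outcome and not an error in the plan.

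**What to change.** In Data analysis, state the answer scale of the perception items. Then:

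- For items with three or more graded answers, compare arms with an analysis that uses the order, preferably a proportional-odds model reporting a common odds ratio with 95% CI, or otherwise Mann-Whitney.
- Count the parent or guardian as the responding unit, not the tooth.
- Keep chi-square for yes/no or unordered items, and keep the frequency tables for all items.

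The cost is a sentence or two of text, with no extra data, visits or participants. The downside is less sensitivity to differences without a direction, such as more answers at both extremes in one arm; the retained frequency tables would still show these.

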### Sequence generation

Teeth will be randomly assigned into one of the groups considering the strata of the research center (UNIB, FOUSP, Uninorte, and UNINOVAFAPI), in 4, 6, and 8 blocks, according to the sequence obtained by an external examiner generated by the website www.sealedenvelope.com.

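### Satisfaction and parents' perception are rated per child but treatment is allocated per tooth: the named two-group tests have no place for a child treated in both arms and can dilute the contrast

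*Protocol article*

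**What the plan says.** All references are to the protocol article.

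- **Unit of allocation.** Study design and ethical aspects: "Teeth will be randomly allocated to selective removal of carious tissue and resin composite restoration (RCR) or NRCC", "with two parallel groups with 1:1 allocation ratio". Sequence generation: "Teeth will be randomly assigned into one of the groups considering the strata of the research center", "in 4, 6, and 8 blocks".
- **Several teeth per child.** Sample selection: "Since each child can contribute with more than one tooth, 20% was added to this value (cluster per child"). Neither the mean nor the maximum number of teeth per child is given. No section assigns all of a child's teeth to one arm or names an index tooth.
- **Who reports, and when.** Discomfort is reported by the child, and the abstract has it measured after each treatment. Satisfaction comes from the child once: "The treatment satisfaction of the participants will be rated using a close-ended questionnaire six months from the initial treatment". Parents' perception of tooth appearance is collected with a questionnaire "applied before the treatment, immediately after, and six months later", and Table 1 shows the same three time points.
- **Analysis.** Data analysis fixes Student's t or Mann–Whitney for discomfort and satisfaction. For parents' perception it says "The data will be summarized as the frequencies. The two groups will be compared using the Chi-Square Test". Within-child correlation is handled only in the shared-frailty Cox model for tooth survival. The intention-to-treat population is defined by participants, although teeth are randomised.

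**The concern.** The named tests compare two independent sets of subjects. With allocation by tooth, a child with two or more study teeth can receive both treatments, and a single six-month rating from that child or parent then cannot be assigned to either arm. The plan does not say what happens to such a record. Entered once per tooth, the same answer sits in both groups and pulls the contrast towards zero.

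The Discussion calls the patient's opinion essential to decision-making. A diluted, non-significant difference in satisfaction or appearance could be misread as equal acceptability.

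**Working it through.** **1. The plan's own figure.** With 89.7% survival in both arms, a margin of 15 points, one-sided 5% and power 80%: n per arm = (1.645 + 0.842)² × 2 × 0.897 × 0.103 / 0.15² = 50.8, so 51, or 102 teeth. Then 102 × 1.2 × 1.2 = 146.9, rounded to 74 per group, 148 teeth. The figure reproduces, but it covers tooth survival only. The 20% for clustering shows that children with several teeth are expected. It does not reveal how many teeth each has, because 1 + (m − 1)ρ = 1.2 fits many pairs of mean cluster size m and correlation ρ.

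**2. Chance that a child is treated in both arms.** Under independent 1:1 allocation this is 1 − 2 × 0.5^k: 0.50, 0.75 and 0.875 for k = 2, 3, 4.

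**3. Dilution.** Assume one rating per child, entered once per tooth, that changes in proportion to the share F of study teeth treated with NRCC. Take a tooth of a child with k study teeth. If it is in NRCC, the expected F is [1 + (k − 1)/2]/k. If it is in RCR, it is [(k − 1)/2]/k. The gap is 1/k: 0.50, 0.33, 0.25 for k = 2, 3, 4. Averaged over all teeth, the retained fraction is children divided by teeth: 1/1.5 = 0.67 at a mean of 1.5 teeth and 1/2 = 0.50 at a mean of 2.

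**4. Effect of blocks.** Two consecutive teeth in a block of size b differ in arm with probability b/[2(b − 1)]: 0.667, 0.600, 0.571 for b = 4, 6, 8. Weighted by block length: (4 × 0.667 + 6 × 0.600 + 8 × 0.571)/18 = 0.60. For k = 2 the retained fraction is therefore 0.40 rather than 0.50.

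**5. Simulation.** 148 teeth, blocks of 4/6/8 drawn at random, a child's teeth in consecutive places, one centre, 1,500 runs per row, child rating entered once per tooth, two-sided 5%. The true all-NRCC versus all-RCR difference is 0.5 SD. The distributions of teeth per child are assumptions.

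| Teeth per child | Children | In both arms | Mean estimate (SD) | Retained | t-test rejects, true 0.5 SD | t-test rejects, no difference |
|---|---|---|---|---|---|---|
| 1 | 148 | 0% | 0.505 | 1.01 | 87% | 4.7% |
| mean 1.5 (60/30/10% with 1/2/3) | 99 | 26% | 0.306 | 0.61 | 44% | 5.1% |
| mean 2 (40/30/20/10% with 1/2/3/4) | 74 | 45% | 0.214 | 0.43 | 23% | 2.5% |
| all 2 | 74 | 60% | 0.201 | 0.40 | 21% | 2.6% |
| all 4 | 37 | 97% | 0.066 | 0.13 | 2% | 1.3% |

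For a dichotomised rating, chi-square rejects in 69%, 31%, 15%, 15% and 2% of runs with the true difference, and in 5.6%, 5.3%, 3.6%, 3.5% and 1.6% with none. Part of the fall in power reflects fewer children, not dilution alone.

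**6. Discomfort.** With a separate score per treated tooth and an assumed within-child correlation of 0.5, the mean estimate in the multi-tooth rows is 0.495 to 0.499 SD. The t-test rejects in 2.5% to 4.2% of runs with no difference and in 86% to 88% with the true difference.

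**7. Pre-treatment answer.** For a continuous score with correlation r between pre- and post-treatment answers, adjustment reduces residual variance by r²: 9%, 25% and 49% for assumed r = 0.3, 0.5, 0.7.

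**The case against.** The strongest reply is that the documents show neither how often children have teeth in both arms nor that one answer is copied to each tooth. The questionnaires are not shown, so their items might refer to a particular tooth, and a full analysis plan might define the unit. The first part stands: mixed-arm children are permitted, not reported. The last does not dispose of the point, because the article names the tests and they do not fit the allocation it describes.

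Several stronger readings are tempting and should not be drawn.

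- **More false positives.** Duplicated records suggest this, but the simulated rates stay at or below about 5%.
- **Bias in discomfort.** It is measured after each treatment, so a score can be tied to one procedure. Only the within-child correlation is ignored.
- **Mixed-arm children contribute nothing.** That would leave 0.25 and 0.125 of the difference for three and four teeth under independent allocation. It treats a 3:1 child and a 1:3 child as alike and overstates dilution if ratings follow the share of teeth treated (0.33 and 0.25).
- **Dilution serves the result the sponsor wants.** Non-inferiority is hypothesised for tooth survival only, and the Discussion hopes for less discomfort with NRCC, which is a difference.
- **The unadjusted test of parents' perception is invalid.** It is not invalid for want of a baseline. Adjustment is a precision gain, of a size the documents do not fix.

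**Conclusion.** The point holds for six-month satisfaction and parents' perception. The tests as named have no place for a child treated in both arms. If the rating is entered once per tooth, about 1/k of the true difference remains for children with k study teeth, and somewhat less under blocks. Over the assumed scenarios with several teeth per child, between 0.61 and 0.13 of the difference is retained. This rests on the rating following the share of teeth treated and on an unstated number of teeth per child; if nearly all children contribute one tooth, the problem is small. The harm is dilution and lost power, not false positives.

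For discomfort the point is lesser: an unbiased estimate from tests that treat correlated scores as independent. For parents' perception, the pre-treatment answer is collected but has no role in the stated test. These are secondary outcomes and the primary analysis is untouched, so the change is advisable rather than critical.

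**What to change.** In Data analysis, state the unit for each outcome and the rule for children treated in both arms:

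- **Satisfaction and parents' perception.** One record per child, all children kept. Model the rating (ordinal or logistic) on the share of the child's study teeth allocated to NRCC, adjusted for number of study teeth and centre. As a sensitivity analysis, compare children whose teeth are all in one arm. That remains a randomised comparison, since all-NRCC and all-RCR are equally likely. It should not be the main analysis, because it drops about 50%, 75% or 87.5% of children with 2, 3 or 4 teeth (more under blocks) and tilts the set towards single-tooth children.
- **Discomfort.** A mixed or GEE model with a child effect, one record per treatment.
- **Post-treatment parents' perception.** Also adjust for the pre-treatment answer.

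The cost is a change of analysis wording, slightly more analysis work, and an assumed dose-like effect of the share of teeth treated. No new data are needed. The model removes the dilution from the estimate and treats each child once; it cannot recover information lost because a mixed-arm child gives only one rating.
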